## Abstract

**Background:**

Sedentary behavior is associated with negative health outcomes. High levels of sedentary behavior are common among Alzheimer disease and related dementias (ADRD) caregivers already at risk of other adverse health effects, yet few interventions target sedentary behavior within this population. There is a need for trials intended to reduce time spent sedentary, which may be achievable by increasing the frequency of disruptions to sedentary time. Remotely delivered behavior change techniques (BCTs) may be effective for disrupting sedentary behavior in this population through short bursts of walking, although it is unclear how BCTs promote this behavior and potentially act via the hypothesized mechanism of behavioral automaticity.

**Objective:**

The goal of the trial is to examine whether a significant proportion of ADRD caregivers (≥50%) receiving an SMS text message–delivered BCT intervention form a habit to engage in hourly walking 4 times per day, with the broader objective of disrupting sedentary time in this population.

**Methods:**

This trial is a 12-week, decentralized, single-arm, National Institutes of Health Stage II behavioral trial. The trial will deliver a personalized, multicomponent BCT intervention to disrupt time spent sedentary by encouraging forming a habit of hourly walking among caregivers of persons with ADRD via the key mechanism of behavior change behavioral automaticity. The intervention includes 4 daily SMS text message–delivered BCT components previously used in interventions to disrupt sedentary behavior—Goal setting, Action planning, Prompts/cues, and Self-monitoring. Formation of an hourly walking habit is the primary outcome and will be defined as walking an additional 250 steps or more per hour for the same 4 consecutive hours as set up in a personalized walking plan on 7 consecutive days. Secondary outcomes include evaluating associations between habit formation and behavioral automaticity, and between longitudinal behavioral automaticity and habitual hourly walking over time. Additionally, heterogeneity of treatment effects will be evaluated. Exploratory analyses will examine potential moderating variables that may influence the intervention effect. The trial uses digital enrollment strategies, SMS text message intervention delivery, passive data collection via Fitbit (Google) devices, and online survey assessments to collect data remotely.

**Results:**

This study was funded by the National Institute on Aging in June 2024. Recruitment and data collection began in March 2025. As of August 2025, 40% (n=40) of the planned sample has been enrolled. Data collection is expected to be complete by June 2026. Data analysis and publication of results are expected by Fall and Winter 2026, respectively.

**Conclusions:**

Results will have the potential to advance knowledge about the effectiveness of BCTs to form a habit of hourly walking and may provide opportunities for future public health impact to promote physical activity in caregivers of those living with ADRD.

## Introduction

The Sedentary Behavior Research Network defines sedentary behavior as “any waking behavior characterized by an energy expenditure ≤1.5 metabolic equivalents, while in a sitting, reclining or lying posture” in adults ≥18 years of age [1]. Examples of sedentary behavior are sitting while working, watching television, or using the computer [2]. According to accelerometer data, US adults spend anywhere from 55% to 86% of their time engaging in sedentary behavior [3-5]. Certain populations are more sedentary than others. Sedentary behavior is particularly common among Alzheimer disease and related dementias (ADRD) caregivers, who make up 26% of the caregiver population in the United States and spend nearly 80% of their waking hours sedentary [6,7]. More time spent sedentary is associated with a higher risk of mortality and morbidity, independent of risks resulting from low physical activity levels [8-11]. There is strong evidence that high levels of sedentary behavior are significantly associated with incidence and mortality due to cardiovascular disease, with incidence of type 2 diabetes, and potentially with incidence of certain types of cancers [11]. High sedentary groups also have a 22% higher dementia risk than low sedentary groups [12,13]. For caregivers, this is particularly concerning given their already elevated risk of negative mental and physical health, poorer quality of life, and worse financial well-being outcomes [14-23]. Given the goal of the National Plan to Address Alzheimer’s Disease to support individuals living with ADRD and their families through caregiver health and well-being promotion, the ADRD caregiver population is a key population for quality interventions targeting sedentary behavior [7,24]. This investment is potentially valuable for both caregivers and those for whom they provide care.

Despite the established need, few interventions in recent literature focus on disrupting sedentary behavior. A meta-analysis of mobile health interventions for physical activity and sedentary behavior in older adults found that only 1 of 33 reviewed studies was designed to target sedentary behavior [25]. Thus, researchers have called for more controlled intervention trials that increase the frequency of interruptions to sedentary time throughout the day, and this is particularly important in targeted populations like caregivers [26-29]. As previous studies have shown that ADRD caregivers prefer to engage in shorter duration exercise (namely, 10-min bouts), incorporating small bouts of behavior changes (eg, walking) into the daily routines of caregivers who are inactive may be a feasible strategy to disrupt sedentary time [29-32]. Some evidence suggests that compared with complex tasks, small, simple actions like this may result in habit formation [33].

Habit formation is theorized to be possible once a stable context (such as time of day or location) allows for a response to repeat enough that the habit is then activated by cues in that context, which can override intention [34-36]. As such, habits are believed to be relatively resistant once formed so long as context is stable [34,35]. Multiple studies have demonstrated successful behavior change with habit formation [37]. Health interventions using behavior change techniques (BCTs) that are rooted in cognitive strategies like reminders and implementation planning are a promising direction for forming habits when paired with stable contexts [35,36]. This is particularly relevant for health behaviors like exercise that require longer-term repetition to result in observable benefits [36].

Behavior change techniques are observable, replicable, irreducible intervention components, thought to be the “active ingredients” to facilitate behavior change [38]. Using BCTs that support the formation of a behavioral habit, such as disrupting sedentary time, may be effective for behavior change [39]. Four BCTs in particular (Goal setting, Action planning, Prompts/cues, and Self-monitoring of behavior) have been previously used in interventions to disrupt sedentary behavior [40-46]. However, there remains a lack of evidence for *how* BCT interventions promote behavior, which is integral to understanding how to optimize and adapt interventions for special populations [47-52]. Given the overlapping features between automaticity and habit, behavioral automaticity is believed to be a possible mechanism of behavior change (MoBC) [37,39,53]. This trial focuses on forming a habit and testing the possible MoBC that causes habit formation using a validated survey assessment; automaticity’s role in *maintaining* a habit may require additional exploration.

Engaging caregivers in longitudinal clinical trial interventions can be challenging [54]. Clinical trials that successfully enroll caregivers exist, although attrition has been a limitation in some [55]. There is a clear need for trials that have considered the unique needs and circumstances of the ADRD caregiver population, such as by using remote trial designs and tailoring for caregivers’ schedules while using high-quality designs rooted in established theories [36,56,57]. Thus, this 12-week remotely delivered decentralized behavioral trial will test the efficacy of a personalized 4-BCT intervention package to form a habit of physical activity as a means of disrupting time spent in sedentary behavior among caregivers of persons with ADRD. This trial uses fully remote strategies for recruitment and enrollment, delivery of text-message interventions, collection of wearable device data via Fitbit (Google) devices, and collection of electronic survey assessments. The trial is informed by habit formation theory, and tests if behavioral automaticity is the key MoBC. The goal of the trial is to examine whether the described BCT intervention is associated with habit formation in ADRD caregivers by walking 4 times a day, reducing levels of overall sedentary time. This trial also addresses gaps in the literature by examining the association between the BCT intervention and habit formation, measured using the potential key MoBC of the walking intervention, behavioral automaticity. Other secondary hypotheses include the timing of behavioral automaticity change and its impact on habit, and the presence of heterogeneity of treatment effects (HTEs) for habit formation and changes in behavioral automaticity. We will also explore moderators of the intervention in exploratory analyses.

## Methods

### Study Design

This fully remote, single-arm, National Institutes of Health (NIH) Stage II decentralized behavioral trial delivering a multicomponent, personalized BCT intervention will enroll 100 caregivers of persons living with ADRD into a 12-week trial comprised of a 2-week baseline period and a 10-week intervention period [58]. The single-arm design of this trial was used to minimize sample size requirements and ensure all eligible caregivers were able to participate in the intervention. Participants will be provided with a Fitbit device for continuous activity tracking and electronic surveys delivered to their smartphones. Fitbit data will be retrieved directly via an Application Programming Interface call. All survey data will be collected and managed using REDCap (Research Electronic Data Capture), a secure, web-based software platform designed to support data capture [59,60]. An overview of the 12-week trial timeline can be seen in Figure 1.

**Figure 1. F1:**
[figure not shown]
Participant timeline. Overview of 12-week trial timeline. BCT: behavior change technique.

### Study Population

Adults (18‐85 y of age), English- and Spanish-speaking caregivers who self-report low levels of physical activity or walking, and those who live in the United States will be recruited to participate. Formal (defined as paid, professional caregivers) and informal (defined as unpaid caregivers) caregivers of persons with ADRD living in the United States will be eligible. Additional inclusion and exclusion criteria are outlined in Textbox 1. Despite our exclusion criteria of smartphone, internet, and email access, we do not anticipate any challenges enrolling a diverse sample. Cross-sectional surveys indicate 91% of Americans own a smartphone, and 82.5% of US caregivers for older adults have smartphones [61,62]. Furthermore, 83.2% of caregivers for adults access the internet and/or use email from a mobile device [63].

Textbox 1.Inclusion and exclusion criteria.
**Inclusion criteria**
Identify as a caregiver (formal or paid, or informal or unpaid) for persons with Alzheimer Disease or Alzheimer disease and related dementiasAge ≥18 and ≤85 yearsSpeak English or Spanish as primary languageSelf-report low levels of physical activity or walking
**Exclusion criteria**
Individuals who self-report having been informed by a clinician it is medically or physically unsafe to engage in a walking interventionDoes not own or cannot regularly access a smartphone capable of receiving SMS text messages or accessing the internetDoes not own or have access to an email addressLives outside the United States

### Recruitment and Consent

Digital recruitment will include email blasts, social media postings, and advertisements in newsletters. Social media platforms, such as Reddit and Facebook (Meta), will also be used to recruit potential participants. In-person recruitment will be conducted in Northwell Health community settings as well as at community events outside of the Northwell Health system. Other recruitment methods may include using the electronic health record to identify individuals with ADRD caregiver status, emails to individuals who previously expressed interest in future research, studies at the Institute of Health System Science, trial listing platforms, and word of mouth.

All study materials (eg, recruitment materials, consent forms, surveys, BCT content, text messages, and other communications) have been translated into US Spanish by a third-party with International Organization for Standardization (ISO) certifications for Quality Management System (ISO 9001:2015) and Language Industry Certification System (ISO 17100:2015), and approved by the Northwell Health Institutional Review Board (IRB). Survey measures for which there is already a validated version in Spanish will be used (described in detail in the Methods section); otherwise, the translated survey from the third-party vendor will be used. At least 2 native Spanish-speaking research team members will review the third-party translations to ensure semantic (eg, ensuring terms and phrases make sense) and idiomatic (eg, ensuring local equivalents for colloquial terms are used) accuracy and dispute any concerns with the third-party translators directly to achieve final translated products. Participants will be asked during screening which language they would prefer to receive study information in. Consenting coordinators who are fluent in the language participants choose (eg, English or Spanish) will conduct research conversations to answer questions and provide clarification about the study.

### Prebaseline Period

After consent, participants will be led to complete a series of digital surveys in REDCap (Figure 2). An onboarding survey will include questions about caregiving and caregiving responsibilities (eg, number of care recipients, relation to person with ADRD, primary caregiver status, length of time providing care, hours providing care per week, and living situation), care recipient characteristics (eg, time since diagnosis and demographic characteristics of person with ADRD), and questions to personalize the study to the caregiver (eg, shipping address, preferred times for contact, and preferred start date). Additionally, participants will complete a digital assessment of caregiver burden (Zarit Burden Interview [64]). After a 2-hour break, participants will receive an SMS text message via a Twilio integration in REDCap (delivered using the Automated Survey Invitations application) with a link to complete a sequence of digital assessments of stress (Perceived Stress Scale [PSS-10] [65,66]), anxiety (State-Trait Anxiety Inventory – short form [STAI-S] [67]), depressive symptoms (adapted version of the Patient Health Questionnaire-9 [PHQ-9] depression module [68]), and quality of life (EuroQol-EQ-5D-5L [69-71], described in more detail in this section). Consenting coordinators will confirm and assign an upcoming baseline start date to participants on a rolling basis. After participants are informed of their start date, they will be mailed a Fitbit device. They will also be automatically sent an SMS text message with a link to REDCap to complete a final set of digital assessments (delivered using the Automated Survey Invitations application) before the baseline period begins—Neuropsychiatric Inventory-Questionnaire [NPIQ] to assess care recipient neuropsychiatric symptoms and associated caregiver distress and Katz activities of daily living (ADLs) to assess care recipients’ ability to perform 6 basic functions independently [72-75]. Participants will receive regular automated SMS text message reminders via REDCap (delivered using the Automated Survey Invitations application) to complete any surveys that are incomplete.

**Figure 2. F2:**
[figure not shown]
Prebaseline digital surveys and activities for consented participants. Katz ADL: Katz Activities of Daily Living; NPIQ: Neuropsychiatric Inventory-Questionnaire; PHQ-9: Patient Health Questionnaire-9; PSS-10: Perceived Stress Scale; STAI-S: State-Trait Anxiety Inventory – Short Form.

### Baseline Period

On the participant’s assigned start date, they will begin a 2-week baseline period to assess adherence to the study protocol and preintervention behavioral automaticity. Participants will not receive any BCTs during the baseline period. Instead, they will engage in their usual level of activity, wear the Fitbit device continuously, and complete weekly SMS text message–delivered surveys via REDCap (delivered using the Automated Survey Invitations application) consisting of the 4-item Self-Report Behavioral Automaticity Index (SRBAI) [76] to assess the MoBC and a single-item assessing overall health from the EuroQol EQ-5D-5L.

To be eligible to continue into the 10-week intervention period, participants must wear their Fitbit for at least 10 hours each day for at least 12 of the 14-day baseline period and must complete one of the 2 weekly surveys. We have successfully achieved desired samples without more-than-expected baseline attrition using similar adherence thresholds used in other remotely delivered behavioral trials [77-80]. Participants who do not meet adherence requirements for the 2-week baseline period will be removed from the study. Figure 3 outlines a timeline of baseline, intervention, and postintervention digital surveys and activities for participants eligible after baseline.

**Figure 3. F3:**
[figure not shown]
Timeline of baseline, intervention, and postintervention digital surveys and activities. BCT: behavior change technique; PHQ-9: Patient Health Questionnaire-9; PSS-10: Perceived Stress Scale; SRBAI: Self-Report Behavioral Automaticity Index.

Before the intervention period begins, participants who successfully meet or exceed the adherence requirements for the 2-week baseline period will complete a short, digital comprehension survey after reviewing an infographic illustrating the intervention phase of the study. Participants who demonstrate understanding by completing the true or false questions accurately and agree to continue to the intervention period will select their preferred 4-hour walking block to walk 250 more steps per hour each day. Participants will have up to 3 days between their baseline period end date and intervention period start date to complete this survey. Participants who do not complete the survey will be contacted by the study team at least 3 times before they are determined to be ineligible to proceed to the intervention period.

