**Figure 4. F4:**
[figure not shown]
Conceptual model linking the behavior change technique intervention, mechanism of behavior change, and primary outcome of habit formation.

Some previous research has shown that caregivers spend 12 (SD 2.8) hours being sedentary per day and receive an average of 7.6 (SD 1.2) hours of sleep per night [6,46]. Spending more than 7 hours per day in a nonsedentary position is associated with a reduced likelihood of developing metabolic syndrome [47]. Furthermore, an additional 250 steps per hour for 4 hours translates to an additional 1000 steps per day, which has been found to have beneficial effects on physical and psychological health in previous research [48-50]. We deduce that 4.4 hours of caregivers’ waking hours are nonsedentary (24-h d –12 h sedentary per d – 7.6 h of sleep per night). Successful disruption of sedentary behavior with 1000 steps per day spread across a 4-hour block (250 steps per h) would result in caregivers achieving an average of over 8 hours of nonsedentary hours per day (4.4 nonsedentary h+4 additional nonsedentary h with successful disruption). This meets the average number of hours per day (>7 h) spent in a nonsedentary position to reduce metabolic syndrome while also meaningfully increasing daily steps and in a feasible manner (eg, in short bursts that disrupt sedentary time).

Below is a definition of each BCT and the delivery timing [38]:

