### Primary Outcome and Analysis

The primary outcome is a binary indicator of habit formation. The goal is to identify whether a significant proportion of caregivers (≥50%) develop habitual hourly walking, thereby disrupting the time they spend sedentary. A participant will have successfully formed a habit of walking if they attain walking 250 steps each hour during their preidentified, preferred 4-hour period each day for 7 consecutive days during the 70-day intervention period (Figure 6). We used this definition of habit to reflect behavioral consistency in physical activity performance. Consistency of physical activity behavior has been found to be a strong correlate of habit in previous research [84]. To ensure that our definition of habit does not bias results, we will conduct sensitivity analyses using 10-day, 14-day, and 21-day periods in addition to the 7-day period used for our primary outcome. We will use a null hypothesis rate of 30% and will compare the achieved proportion of habit formation versus this null level, using a 1-sample binomial test with a 2-sided α at 5%. The rate of habit formation will be summarized using the observed proportion along with a 95% CI. We will also use Kaplan-Meier curves to identify estimates of the time-to-event for habit formation in the sample.

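### Neither entry nor the freely chosen 4-hour block is tied to low-activity hours, so forming the habit does not by itself show that sedentary time was disrupted

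*Protocol article*

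**What the plan says.** All references are to the protocol article.

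- **Entry.** Study Population and Textbox 1 admit caregivers, paid or unpaid, who "self-report low levels of physical activity or walking". No step or sedentary-time threshold is stated.
- **Baseline gate.** Baseline Period describes a "2-week baseline period to assess adherence to the study protocol and preintervention behavioral automaticity". To continue, "participants must wear their Fitbit for at least 10 hours each day for at least 12 of the 14-day baseline period", and one of the two weekly surveys must be completed. A comprehension survey follows. None of these conditions concerns activity level.
- **Choice of block.** At the end of Baseline Period, participants who pass "will select their preferred 4-hour walking block to walk 250 more steps per hour each day". Under BCT Intervention, staff check the entered times against the survey for accuracy only.
- **Rationale.** BCT Intervention, Overview, starts from earlier research in which "caregivers spend 12 (SD 2.8) hours being sedentary per day and receive an average of 7.6 (SD 1.2) hours of sleep per night". It continues: "We deduce that 4.4 hours of caregivers’ waking hours are nonsedentary". The expected gain is written as "4.4 nonsedentary h+4 additional nonsedentary h with successful disruption", which is set against a benchmark of more than 7 nonsedentary hours a day.
- **Objective.** Primary Outcome and Analysis asks whether at least half of caregivers "develop habitual hourly walking, thereby disrupting the time they spend sedentary".
- **Scope.** Principal Results leaves objective confirmation of sedentariness to later work. Potential Limitations discusses standing breaks and the habit definition, but neither block choice nor baseline activity.

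**The concern.** The step from a walking habit to less sedentary time needs the habit to fall in hours that were previously inactive. Three rules could secure this: entry, the baseline gate and block selection. The article states all three, and none refers to measured activity. The trial has a single arm and does not measure sedentariness objectively, so the primary result cannot separate a habit formed in inactive hours from one formed in hours that already held walking.

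At stake is the interpretation of the result. A habit rate above the 30% null could be reported as disruption of sedentary time without any evidence on what the chosen hours looked like before.

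**Working it through.** **Inputs** (BCT Intervention, Overview): 12 h sedentary and 7.6 h sleep per day; a 4-hour block; a benchmark of more than 7 nonsedentary hours.

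**1. The plan's own figure.** 24 − 12 − 7.6 = 4.4 nonsedentary waking hours. 4.4 + 4 = 8.4 h, which agrees with the stated average of over 8 h.

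**2. The condition behind it.** Let s be the number of block hours that were sedentary before the intervention. I keep the plan's convention that a successful block hour counts as a whole nonsedentary hour. Only previously sedentary hours add to the total, so the total is 4.4 + s.

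| s (of 4) | Nonsedentary h/day | Above 7 h? |
|---|---|---|
| 4 | 8.4 | yes |
| 3 | 7.4 | yes |
| 2.6 | 7.0 | break-even |
| 2 | 6.4 | no |
| 1 | 5.4 | no |
| 0 | 4.4 | no |

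Break-even is s = 7 − 4.4 = 2.6, and 2.6 / 4 = 65% of the block. The plan's 8.4 h is the case s = 4.

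**3. A neutral reference.** Assume the block falls at random over the waking day. Waking time is 24 − 7.6 = 16.4 h, of which 12 / 16.4 = 73% is sedentary. Then s = 4 × 12 / 16.4 = 2.93 and the total is 4.4 + 2.93 = 7.33 h. The benchmark is still passed, but the margin falls from 8.4 − 7 = 1.4 h to about 0.3 h. Block choice moves the total up or down from there, and the article gives no figure for the direction.

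**4. Can existing data fill the gap?** Yes, for steps. The Fitbit is worn for 14 days before any message is sent, and the block is chosen after that. Usual steps in each chosen hour can therefore be computed for everyone who reaches the intervention, including those already enrolled.

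**5. Price of a restricted analysis.** Taking an observed rate of 50% as an illustration, the normal-approximation 95% half-width is 1.96 × √(0.25 / n). For the planned n = 60 it is 12.7 percentage points. If half of them qualified (n = 30, an assumed share), it would be 17.9 points.

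**The case against.** The strongest defence is that the primary outcome is habit formation. Disrupting sedentary time is the broader objective, and its objective confirmation is declared out of scope. Free choice of block is deliberate: habit theory asks for a stable context, and caregivers' schedules call for tailoring. Eligibility is applied through a staff-reviewed screening questionnaire whose items are not shown. All of this stands as a defence of the design. It does not cover the wording of the objective, which derives disruption from the habit, or the 8.4 h rationale.

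Several stronger readings are tempting, but the article does not support them:

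- **Caregivers will pick hours when they are already moving.** Nothing says so. Because they are asked for extra steps, they could as easily pick quiet, seated hours.
- **A whole block fits inside active time because 4.4 h exceeds 4 h.** The 4.4 h is a daily total, not one continuous stretch.
- **About 16% of caregivers have at least 7.2 nonsedentary hours** (one SD: 24 − 9.2 − 7.6). This assumes normality, fixes sleep at its mean and applies a cited sample's SD to a trial that screens for low activity. Such a person still has 9.2 sedentary hours to interrupt.
- **Extra steps in an active hour interrupt nothing.** This is too absolute, since an hour with several hundred steps can still contain sitting.
- **The primary test is biased towards success.** That would need a share of participants who already meet the target, which the article does not give. It would also need scoring on total steps. The article words the outcome both as total and as additional steps, which is a separate matter to reconcile; under additional-step scoring this route largely disappears.

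**Conclusion.** The gap is real and concerns what may be concluded. Entry, baseline gate and block choice leave the activity level of the chosen hours open, while the rationale and the wording of the objective take it as given. The 8.4 h figure requires all 4 block hours to have been sedentary, and reaching 7 h requires at least 2.6 of them. These figures rest on the cited averages and on the plan's whole-hour counting.

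The number of participants or hours affected is not given and may be small, and the loss of interruption may be partial. The point therefore does not show that the habit result would be wrong or that the wrong people are being enrolled. It shows that the statement about sedentary time lacks support that the trial's own baseline data could partly supply.

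**What to change.** 1. For each participant, compute the usual (for example median) baseline steps in each of the four chosen clock hours, using days on which the device was worn in that hour. Report the distribution and the number of block hours below 250.
2. Before analysis, prespecify a sensitivity analysis of the primary outcome restricted to participants whose block hours were all usually below 250 steps at baseline. Give the proportion with its 95% CI next to the full-sample result.
3. In Primary Outcome and Analysis, limit the statement that the habit disrupts sedentary time to what this analysis supports. Say that a low step count cannot tell sitting from standing. Add block choice to Potential Limitations.
4. Optionally, show future participants their own low-step hours when they choose the block, as guidance only.

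A new exclusion is not advised. If every hour in a block had to be below 250 steps, one 250-step hour in every four would rule out all blocks. Over 16 waking hours that is 4 × 250 = 1,000 steps a day, so very inactive caregivers could be lost. With 40 of 100 enrolled by August 2025, a new gate would also mix two populations.

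Cost: a short analysis of data already held and a smaller subset with a wider interval. Item 4 also changes participant materials and would go to the IRB.
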